### Recruitment & randomization

From among these same ≥ 200 patients, our team will partner with the patients’ primary care providers (PCPs), hematologists, or oncologists to recruit and consent 200 adult cancer survivors for clinic visits and focus groups for the remainder of the study. The study team members will contact each potential patient to gauge their interest to participate in the study. Potential study participants who exhibit interest and/or agree to enroll in the study will be provided an information packet containing an informed consent form that offers a more in-depth description of the study and contact information if they are to have additional questions. Those who do not express interest in the study will be noted and no longer contacted. Study participants will be randomly distributed into either the Clinical Decision Aid Group (where *N* = 100 patients will use the clinical decision aid in addition to current practice) or the Control Group (where *N* = 100 patients will only have access to current practice) based on the following stratification factors: sex and race/ethnicity. In collaboration with our biostatistician, patients will be randomly distributed into one of these two arms based on the following stratification factors: sex (2: male, female) and race/ethnicity (3: White, Black, other).

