### Primary endpoints

Chart reviews will also be completed for all patients to assess medication use and imaging patterns in accordance with cardio-oncology recommendations at three and six months after the baseline clinic visit, as the primary endpoints.

If the patient chooses not to or is unable to pursue the recommendations suggested by the clinical decision aid as discussed by the physician, this would be noted in the chart. Therefore, if the physician offers the recommendation, this will be considered consistent with the society statements, even if the patient chooses not to follow the recommendation. An adjudication committee of 3 people may be established to decide what is considered consistent with evidence-based recommendations. If 2 of 3 people agree, that would be considered consistent with evidence-based recommendations.

Success will be determined by ≥ 85% of clinic visits using the clinical decision aid resulting in pursuit of medication use and cardiac imaging surveillance patterns commensurate with recommendations specific to cancer survivors, with overall rates the same or higher than the group without the clinical decision aid, as well as overall favorable patient and physician focus group comments and survey responses.

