### Statistical methods

#### Sample size and power analysis

Assuming 40% consistency with evidence-based recommendations at baseline for both groups [18, 20, 40], we will consider clinical significance at a 50% increase from baseline, which corresponds to 60% consistency with the recommendations. To go from 40% at baseline to 60% in the intervention arm of the trial (i.e., Clinical Decision Aid group) with 80% power requires 97 patients in each group, or 194 total patients. We may be powered to detect such a clinically reasonable change in the primary endpoint. Although we may be powered for this modest change, we could also consider a greater increase from baseline. To go from 40 to 85% with 80% power requires 17 patients in each group, or 34 total patients. We would also be powered for this, but this increase may not be reasonably obtainable.

In this feasibility study, the total number of patients will be limited to 200. One cohort of 100 patients will have clinic visits with current practice plus the clinical decision aid. The other cohort of 100 patients will have clinic visits with current practice alone. This should allow for capturing a variety of cancers and include ethnic minorities in each group.

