### Data analysis

We will compare the following measurements between the Clinical Decision Aid Group and the current practice only Control Group: baseline characteristics, perceptions and attitudes toward decision-making in the clinic visit, medication initiation (e.g., statins or beta blockers for cardioprotection), cardiovascular lab testing obtained, physical activity pursued (based on survey responses), cardiovascular imaging tests ordered or recommended for surveillance. We will also analyze data using qualitative descriptive statistics for focus group results from patients and clinicians in the Clinical Decision Aid Group.

Scores will be calculated for individual survey questions, with a higher number indicating a more favorable response. The randomization groups will be considered as the independent variables and survey scores, as well as short-term outcome measures, such as cardiovascular medication initiation and imaging parameters, and lab test results if applicable, as the dependent variables. Survey scores, imaging parameters, medication use, and lab tests if applicable, will be compared between the group of patients that use the clinical decision aid (Clinical Decision Aid Group) and the group of patients that do not use the clinical decision aid (Control Group) at single visits (baseline, three months, six months). Additionally, survey scores for information seeking and sharing, as well as imaging parameters and medication use, and lab tests if indicated, will also be compared between the Clinical Decision Aid Group and the Control Group between visits. Thus, changes over time in the Information Seeking and Sharing survey responses, imaging parameters, medication use, and lab tests if results applicable, will be investigated. We will assess whether survey responses, imaging parameters, medication use, and lab tests if applicable, differ by study group (Clinical Decision Aid Group versus Control Group) or by risk-stratified patient similarity cluster. We may also pursue subgroup analyses to compare clinical decision aid and Control Group results within each patient similarity risk cluster, between races, or by sex.

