Simple group comparisons will be made using the chi-square or Fisher’s exact test as appropriate for binary survey score variables. Logistic regression will also be used to estimate the effect of the randomized group on the binary score for each survey question, to allow us to adjust data for the following baseline socioeconomic demographics: age, sex, and level of education if known. These demographic characteristics will also be investigated as potential predictors using multivariate analyses, for survey questions or short-term outcomes with results significantly different between the two randomized groups. Continuous variables will be expressed as mean with standard deviation, whereas dichotomous variables will be expressed as percentages. For continuous characteristics or outcomes, Wilcoxon rank sum test or two-sample t-test will be used as appropriate. Statistical data will be expressed as odds ratio with confidence interval or mean with standard error. Statistical significance will be accepted as *P*-value of < 0.05.

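### Randomisation is stratified by sex and race/ethnicity, but the stated covariates omit race/ethnicity, and no stratification-adjusted treatment effect is stated for the medication and imaging outcomes

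*Protocol article*

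**What the plan says.** Under *Recruitment & randomization*, patients are allocated 100 per arm "based on the following stratification factors: sex (2: male, female) and race/ethnicity (3: White, Black, other"), which gives 2 × 3 = 6 strata.

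Under *Data analysis*, three statements matter:

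- The adjusted model is defined for survey items: "Logistic regression will also be used to estimate the effect of the randomized group on the binary score for each survey question". Its purpose is to "adjust data for the following baseline socioeconomic demographics: age, sex, and level of education if known". Sex is in the list; race/ethnicity is not.
- The same demographics are then examined as possible predictors, but only "for survey questions or short-term outcomes with results significantly different between the two randomized groups".
- The short-term outcomes are "short-term outcome measures, such as cardiovascular medication initiation and imaging parameters", with laboratory results where applicable.

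Under *Primary endpoints*, chart review will "assess medication use and imaging patterns in accordance with cardio-oncology recommendations at three and six months after the baseline clinic visit". The outcomes reached only through the significance condition are therefore the ones on which the primary endpoints rest.

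Race returns in the analysis text once more, as an option: "subgroup analyses to compare clinical decision aid and Control Group results within each patient similarity risk cluster, between races, or by sex". Table 1 lists race and ethnicity as baseline characteristics. It does not list education.

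**The concern.** A trial that balances its arms on a factor should normally analyse by that factor. Stratified allocation removes chance imbalance in the factor, so the true variance of the arm difference is smaller than an unstratified test assumes. If the factor predicts the outcome, that test is too cautious and some power is lost. Here one stratification factor is carried into the stated model and the other is not, without a reason given. The omitted factor is certain to be available, while one that is included (education) carries the protocol's own doubt about whether it will be known.

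The second part concerns where covariates are used. For medication and imaging they enter only once the unadjusted result is significant, and then as predictors. The primary outcomes are thus left without a stated effect estimate that reflects how patients were randomised. At stake is precision on the outcomes that matter most, in a trial planned close to 80% power.

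**Working it through.** **1. The plan's own sample size.** Inputs from *Sample size and power analysis*: "Assuming 40% consistency with evidence-based recommendations at baseline for both groups", 60% in the intervention arm, 80% power. *Data analysis* gives the 0.05 level; sidedness is not stated, so two-sided is assumed. With pooled variance and no continuity correction:

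n = [1.960·√(2·0.5·0.5) + 0.842·√(0.4·0.6 + 0.6·0.4)]² / 0.20² = (1.386 + 0.583)² / 0.04 = 96.9, so 97 per group.

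For 40% against 85%: (1.342 + 0.510)² / 0.45² = 16.9, so 17 per group. Both stated figures reproduce. They come from an unadjusted comparison, whose power is 80.0% at 97 per arm and 81.2% at 100 per arm.

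**2. Covariates against strata.**

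| Factor | Stratifies randomisation | In the adjusted survey model | In Table 1 |
|---|---|---|---|
| Sex | yes | yes | yes |
| Race/ethnicity | yes | no | yes |
| Age | no | yes | yes |
| Education | no | if known | no |

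**3. What ignoring the strata does.** Let R² be the share of outcome variance explained by the strata. With arms balanced within strata, the true variance of the arm difference is about (1 − R²) times what the unadjusted test uses. Its actual two-sided size is then about 2·[1 − Φ(1.96/√(1 − R²))], which cannot exceed 5%.

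**4. Simulation.** 200 patients, permuted blocks of 4 within the 6 strata, 3000 runs per cell, 40% overall in control and 60% under the alternative. Assumed, because the article gives no such figures: 70% women; 70/20/10% White/Black/other; log-odds effects of sex and of race as listed (Black against White, with half that effect for other).

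| Assumed effect (sex, race) | Type I error: unadjusted / sex / sex + race | Power: unadjusted / sex / sex + race |
|---|---|---|
| none (0, 0) | 0.055 / 0.054 / 0.055 | 0.832 / 0.830 / 0.827 |
| moderate (0.4, 0.7) | 0.052 / 0.052 / 0.052 | 0.837 / 0.835 / 0.836 |
| strong (0.8, 1.4) | 0.041 / 0.040 / 0.048 | 0.825 / 0.824 / 0.842 |
| very strong (1.2, 2.0) | 0.029 / 0.032 / 0.045 | 0.852 / 0.857 / 0.885 |

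Check of the last row against step 3. The implied control rates for White/Black/other are 0.295/0.054/0.133 in men (weights 0.21/0.06/0.03) and 0.582/0.158/0.338 in women (weights 0.49/0.14/0.07). The between-stratum variance Σw(p − 0.4)² is 0.036, so R² = 0.036/0.24 = 0.15. The size is 2·[1 − Φ(1.96/√0.85)] = 2·[1 − Φ(2.13)] = 0.033, in line with the simulated 0.029 (Monte Carlo standard error 0.003).

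The loss from omitting race alone is the gap between the sex column and the sex + race column. It is nil for no or moderate effects (0.830 to 0.827; 0.835 to 0.836), 1.8 points for strong (0.824 to 0.842) and 2.8 points for very strong (0.857 to 0.885).

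**5. A more extreme case.** A second set of 4000 runs compared the unadjusted test with Cochran-Mantel-Haenszel over the 6 strata. With assumed race-specific rates of 70/20/30% under the null, type I error was 2.6% against 4.5%. With control rates of 65/15/25% and a 20-point effect, power was 85.8% against 90.8%, a gap of 5.0 points. With a weaker race effect (50/25/35%), power was 83.4% against 83.7%. The race shares behind this set are not stated, so it serves only to illustrate the upper end.

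**The case against.** The best reply is that little is lost and that some of the plan can be read too harshly. Most of this stands.

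- **Only-winners reporting.** A reader might infer that adjusted effects appear only for significant results. The document does not support that. The survey logistic model runs whatever the unadjusted result. The conditional step is a search for predictors, not an adjusted treatment effect. Medication and imaging are compared between arms at each time point and between visits regardless of significance, so no comparison is suppressed.
- **Loss of patients through education.** A reader might infer that patients with unknown education are dropped. No complete-case rule is stated, and the qualifier may mean only that the variable is used if it is available. With 20% unknown, a complete-case fit would keep 0.8 × 200 = 160 patients, but both the 20% and the rule are assumptions.
- **Invalid inference.** Omitting the factor causes neither bias nor excess false positives. Simulated unadjusted power stays above 80% in every scenario shown.
- **Feasibility aim.** Success is defined by an 85% concordance threshold, rates no lower than control and favourable feedback. It is not stated as a significance test, so a small loss of precision does not alter that criterion.
- **Condensed article.** A full analysis plan may contain an adjusted primary model, and its absence here would not by itself be a fault.

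What remains is that the article does fix a covariate list, and that list departs from its own randomisation. It also fixes when covariates reach the medication and imaging outcomes. An analysis plan that follows the article would carry both forward. The optional subgroup look by race does not substitute for a stratification covariate.

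**Conclusion.** The point holds as a matter of precision. One of the two stratification factors is missing from the stated covariates, and no stratification-adjusted treatment effect is stated for the primary medication and imaging outcomes. The power cost is between 0 and about 5 points: nothing under moderate assumed effects, and about 3 to 5 points only when race/ethnicity is very strongly prognostic. In that case the actual type I error of the unadjusted test falls to about 3%. These sizes rest on assumed race shares and race-specific rates, because the article gives none. The direction does not depend on them: the unadjusted test can be conservative but not anti-conservative. The stated sample size is unaffected.

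**What to change.** For the primary concordance outcome and for each survey outcome, prespecify one treatment-effect model with randomised group, sex, race/ethnicity (3 levels) and age, fitted whatever the unadjusted p-value. A Cochran-Mantel-Haenszel test over the 6 strata is an acceptable alternative. Keep the significance-conditioned predictor analysis, if it is wanted, as a separate exploratory step. If education stays in the model, carry unknown as its own category so that no randomised patient is dropped.

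The cost is about a sentence in the analysis plan, settled before outcomes are examined. It needs no new data, since sex and race/ethnicity are recorded for randomisation and age is in Table 1, and no change to the sample size.

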### Study population

The overall study cohort dataset of > 4,000 individuals includes demographic, physiological, laboratory, medication, medical history, and outcomes data relevant to cardiovascular risk stratification in individuals with a history of cancer, as well as cardiovascular imaging reports [30]. This cohort will be queried to identify ≥ 200 adult cancer survivors (including ethnic/racial minorities) clinically considered to be at intermediate, high, or very high cardiovascular risk following cancer therapy determined imprecisely based on demographic and comorbidity information [3, 11, 31–34].

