### Secondary endpoints

Survey responses will be reviewed to determine the impact of the use of the clinical decision aid, in addition to current practice, on cancer survivors’ perceptions of the tool and heart health-related behaviors. The percentages of favorable survey responses and scoring tool results in the patient group using the clinical decision aid will be compared to results from the patient group that does not use the clinical decision aid. A high score will indicate favorable responses for a particular survey, demonstrating favorable perception of the tool regarding the survey topic. We anticipate ≥ 80% of survey questions scored favorably by the group of patients who use the clinical decision aid, with scores the same or higher than the group without the clinical decision aid [39].

Clinically indicated lab values such as troponin, NT-pro-BNP, potassium, and lipid panel, along with BMI, will also be reviewed.

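### Continuous lab results are compared by unadjusted tests, at each visit and again between visits, without using the patient's earlier value where there is one

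*Protocol article*

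**What the plan says.** All of this comes from the protocol article.

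- **Test.** Data analysis gives one rule for continuous data: "For continuous characteristics or outcomes, Wilcoxon rank sum test or two-sample t-test will be used as appropriate".
- **Comparisons by visit.** Lab test results are among the dependent variables, and the arms are compared "at single visits (baseline, three months, six months").
- **Comparisons between visits.** The same section adds that "lab tests if indicated, will also be compared between the Clinical Decision Aid Group and the Control Group between visits". It says of changes over time, including in "lab tests if results applicable, will be investigated", but attaches no test to them.
- **Which values.** Secondary endpoints states: "Clinically indicated lab values such as troponin, NT-pro-BNP, potassium, and lipid panel, along with BMI, will also be reviewed".
- **Adjustment.** Logistic regression for the binary survey scores adjusts for age, sex and level of education. The same demographics enter multivariate analyses of survey questions or short-term outcomes, but only where the arms have already been found to differ significantly.
- **Significance.** P < 0.05 is the single threshold.
- **Earlier values.** Study population says that the cohort dataset "includes demographic, physiological, laboratory, medication, medical history, and outcomes data relevant to cardiovascular risk stratification". Table 3 lists potassium and BMI among the algorithm inputs. Troponin, NT-proBNP and a lipid panel are not listed there.

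**The concern.** A lab value usually resembles the same patient's previous value. A two-sample test at three or six months ignores this and leaves the predictable part of the variation between patients in the error term. Subtracting the earlier value goes too far the other way: it fixes the slope on that value at 1, which adds noise when the correlation is below 0.5. ANCOVA estimates the slope. In large samples, and with equal variances at the two visits, it is more precise than either test for any correlation strictly between 0 and 1.

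A value taken at or before the baseline visit cannot have been changed by the decision aid, so it is a sound covariate. Two things are at stake. One is precision on the continuous lab outcomes. The other is a clear reading of them: the level and change comparisons address the same effect and can disagree when the arms differ by chance at baseline. Randomisation is stratified by sex and race/ethnicity, which does not prevent such imbalance in a lab value.

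**Working it through.** **The plan's own figure.** The only sample size in the article is for the binary primary endpoint. With pooled variance, two-sided 0.05 and 80% power:

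- 40% v 60%: n = [1.96 × √(2 × 0.5 × 0.5) + 0.842 × √(0.24 + 0.24)]² / 0.20² = (1.386 + 0.583)² / 0.04 = 96.9, so 97 per group, as stated.
- 40% v 85%: the same formula gives 17 per group, as stated.

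Both figures reproduce, and nothing below changes them. The article states no power for any continuous outcome.

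**Inputs for the lab comparison.** 100 per arm (Sample size and power analysis) is used as an upper bound, because labs are taken only when indicated. The threshold is 0.05, taken as two-sided, which is what reproduces the 97. The correlation r between the earlier and the follow-up value is not in the article, so 0.3, 0.5 and 0.7 are assumptions. Variances are in units of SD² and assumed equal at the two visits. The test of change is taken to be the two-sample test, because the article names no other method for continuous outcomes.

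**Variance of each analysis.** Single visit: 1. Change: 2(1 − r). ANCOVA: 1 − r².

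| r | Single visit | Change | ANCOVA | Single / ANCOVA | Change / ANCOVA |
|---|---|---|---|---|---|
| 0.3 | 1 | 1.40 | 0.91 | 1.10 | 1.54 |
| 0.5 | 1 | 1.00 | 0.75 | 1.33 | 1.33 |
| 0.7 | 1 | 0.60 | 0.51 | 1.96 | 1.18 |

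**Power.** The effect that a single-visit test detects with 80% power at 100 per arm is (1.96 + 0.842) × √(2/100) = 0.396 SD. Power for an analysis with variance v is Φ(2.802/√v − 1.96).

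| r | Single visit | Change | ANCOVA |
|---|---|---|---|
| 0.3 | 80% | 66% | 84% |
| 0.5 | 80% | 80% | 90% |
| 0.7 | 80% | 95% | 98% |

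Put as sample size, ANCOVA matches a single-visit test on 100 per arm with 100 × (1 − r²) = 91, 75 and 51 per arm. With fewer patients the absolute power falls, but the variance ratios for patients with both values stay the same.

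**False positives.** Under no effect, the single-visit and change statistics have correlation √((1 − r)/2) = 0.59, 0.50 and 0.39. In simulation (2 million draws), at least one of the two gives P < 0.05 in 8.7%, 9.1% and 9.3% of cases for one outcome at one time point. Counting level and change at both three and six months, assuming the same correlation r between all visits, the figure is about 16% (15.9%, 16.1% and 15.9%).

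**The case against.** The strongest case against is that little depends on these outcomes and that much of the detail is inferred.

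- **Availability.** A reader might infer that every patient's earlier value is collected. The article does not establish this. Labs are qualified throughout as clinically indicated or if applicable, three of the four labs named under Secondary endpoints are not algorithm inputs, and the description of the cohort dataset does not say which labs are held, for whom or how recent. This stands: the gain applies only to patients with both values, and an old value may correlate weakly.
- **BMI.** A reader might infer that BMI is also tested at each visit and as change. It is only to be reviewed and is absent from the lists of comparisons in Data analysis. Only the general sentence on continuous outcomes reaches it.
- **Adjustment.** It would be wrong to say that the survey logistic model is the only adjusted analysis. A demographic adjustment for short-term outcomes exists. It follows a significant result, however, so it cannot recover lost power, and it does not use the earlier value.
- **Test of change.** Its use here is inferred, and a separate analysis plan may give more. The point does not rest on that silence: the article fixes an unadjusted test for continuous outcomes, and the single-visit comparisons fall under it directly.
- **Size.** Against the better of the two planned tests, the gain is 4, 10 and 3 percentage points at r = 0.3, 0.5 and 0.7. That is fair. But the plan does not say which test is to be preferred, and the better one depends on r.
- **Follow-up testing.** Follow-up visits occur as clinically indicated, and whether lab testing was obtained is itself compared between arms. Having a follow-up value may therefore depend on arm. ANCOVA does not correct this.

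**Conclusion.** The point holds for continuous lab results, and it is minor. The article names an unadjusted method where a baseline-adjusted one would be more precise for patients with both values. The direction does not depend on the assumed correlation as long as it lies strictly between 0 and 1. The size does: 1.10 to 1.96 times the ANCOVA variance for the single-visit test, and 1.18 to 1.54 times for change, over r from 0.3 to 0.7. The power figures also assume 100 per arm with values, which is probably too many by an amount the article does not let one estimate. Level plus change at one time point carries about a 9% chance of at least one false positive.

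A reader might infer that the trial's main conclusion is weakened. The article does not support that. The primary endpoint is binary consistency with recommendations, the success criterion under Primary endpoints uses no lab value or BMI, and the sample size rests on proportions.

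**What to change.** For each continuous lab outcome, at three and at six months, use one ANCOVA of the follow-up value on randomised arm and the patient's last value at or before the baseline visit. Use the log scale for skewed markers such as troponin and NT-proBNP. Report the adjusted difference (a ratio, if back-transformed from the log scale) with its 95% confidence interval. Keep the single-visit and between-visit comparisons as description, without tests. If BMI is to be formally compared, apply the same model to it.

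State a rule for patients with no earlier value, for example mean imputation of the covariate. Beside each result, show the number of patients with a follow-up value in each arm, so that the reader can see whether testing differed by arm.

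The cost is a change of wording, with no new data. The limits are that fewer than 100 patients per arm are likely to contribute, that the missing-baseline rule has to be fixed in advance, and that an adjusted estimate can look more secure than it is if follow-up testing differs between the arms.
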